### Statistical analysis

All analyses will follow the intention-to-treat principle. Statistical tests will be two-sided with a significance level of 0.05 unless otherwise specified. Analyses will be performed using R (version 4.3.1 or later).

The primary outcome is the change from baseline to Week 6 in the combined relative abundance of five prespecified butyrate-producing taxa. The between-group difference will be assessed using a two-sample t-test or Mann–Whitney U test depending on distributional assumptions. ANCOVA adjusting for baseline values will be performed as a prespecified supplementary analysis. Because 16S rRNA gene sequencing data are compositional, a sensitivity analysis of the primary outcome using centred log-ratio transformation will be performed.

Secondary continuous outcomes will be analysed using ANCOVA models adjusting for baseline values. Repeated measures will be analysed using linear mixed-effects models with random intercepts to account for within-participant correlations and to evaluate time-by-group interactions.

Microbiome sequencing data will be processed using the QIIME 2 [13,14] platform. Taxonomic assignment will be performed using a prespecified reference database and classifier. Because species-level classification by 16S rRNA gene sequencing may be limited for some taxa, the primary analysis will use the most resolved taxonomic level that can be reliably assigned by the sequencing region and classifier. Taxa corresponding to the prespecified butyrate-producing bacteria will be aggregated according to a predefined taxonomic mapping before unblinding. Alpha diversity indices will be compared using parametric or non-parametric tests as appropriate. Beta diversity will be analysed using PERMANOVA based on UniFrac and Bray–Curtis distance matrices. Differential abundance analysis will be performed using LEfSe [15], with ANCOM-BC and/or ALDEx2 used as complementary approaches to account for the compositional nature of microbiome data. For multiple related comparisons, particularly microbiome taxa analyses, short-chain fatty acid comparisons, and immunological marker panels, false discovery rate correction using the Benjamini-Hochberg procedure will be applied. Adjusted p values will be reported alongside unadjusted p values where applicable.

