Exploratory analyses, including changes in individual taxa, microbiome-immune correlations, Treg phenotypic subset analyses, and responder versus non-responder comparisons, will be considered hypothesis generating. Dietary intake data from the daily dietary record will be summarised descriptively.

The primary analysis will include all randomised participants with available baseline and Week 6 primary outcome data, according to the intention-to-treat principle. Missing outcome data will be examined for patterns and likely mechanisms. If missingness is judged to be at random, multiple imputation using chained equations will be performed as a sensitivity analysis. Adverse events will be summarised descriptively by treatment group. No interim analyses are planned.

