### Safety monitoring

Adverse events (AEs) will be recorded throughout the study period. An AE is defined as any unfavourable or unintended disease, sign, symptom, or abnormal laboratory finding occurring in a participant, regardless of its causal relationship with the study. Expected AEs related to the study products include diarrhoea, soft stools, abdominal bloating, and food allergy; the risk of these events is considered low. Blood samples of 40 mL before the intervention and 60 mL immediately after the intervention will be collected for immunological analyses, and the risk of anaemia is considered very low. If an AE occurs, the investigators will provide appropriate medical care and record the event in the medical records. The study product may be discontinued if necessary. Participants may be withdrawn if they request withdrawal, become ineligible after enrolment, experience an AE or worsening of symptoms that makes continuation inappropriate, substantially deviate from the protocol, fail to comply with the intervention, or if the principal investigator judges that continuation is difficult. Participants who discontinue the study product will be asked to continue scheduled follow-up assessments where possible.

Trial continuation will be reviewed if important safety or efficacy information becomes available, recruitment is judged to be extremely difficult, the study objective is achieved before the planned sample size or study period is reached, or protocol changes requested by the ethics committee cannot be implemented. If the ethics committee recommends or instructs termination, or if the principal investigator decides to suspend or terminate the study, the reason will be promptly reported to the ethics committee and the head of the study institution.

In the event of study-related harm, medical care will be provided through the usual health insurance system.

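### The primary analysis is labelled intention-to-treat but uses only participants with both samples, and its one missing-data sensitivity analysis depends on an unverifiable judgement

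*Protocol article*

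**What the plan says.** The Statistical analysis section of the protocol article opens with a general rule: "All analyses will follow the intention-to-treat principle". For the primary outcome, the change from baseline to Week 6, it states: "The between-group difference will be assessed using a two-sample t-test or Mann–Whitney U test depending on distributional assumptions". A change score needs both samples, and the end of the section makes this explicit: "The primary analysis will include all randomised participants with available baseline and Week 6 primary outcome data, according to the intention-to-treat principle".

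On missing data there are two further sentences: "Missing outcome data will be examined for patterns and likely mechanisms", and then "If missingness is judged to be at random, multiple imputation using chained equations will be performed as a sensitivity analysis". Nothing follows for the case in which missingness is judged not to be at random.

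One other sensitivity analysis of the primary outcome is named ("a sensitivity analysis of the primary outcome using centred log-ratio transformation will be performed"). The section justifies it by the compositional nature of sequencing data, so it does not address missing outcomes.

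The Safety monitoring section bears on why data might be missing. It says: "Expected AEs related to the study products include diarrhoea, soft stools, abdominal bloating". The same sentence goes on to add food allergy and to rate the risk as low. Participants may be withdrawn if they "experience an AE or worsening of symptoms that makes continuation inappropriate, substantially deviate from the protocol, fail to comply with the intervention", among other reasons. Those who stop the product are to be asked to keep attending assessments where they can.

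**The concern.** Two things are fixed badly.

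**The label.** A set defined by having both samples is not the set of all randomised participants. Analysing observed participants in the arm to which they were assigned is common and defensible, but calling it intention-to-treat without qualification tells the reader that nobody was left out. The results paper would inherit that description.

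**The condition on imputation.** Whether missingness is at random, given what was observed, cannot be verified from the observed data. Patterns and recorded reasons can make the assumption more or less plausible, but they cannot settle it. The plan lets this judgement, made after the data are in and without a stated criterion, decide whether the only missing-data sensitivity analysis exists at all. If the judgement goes the other way, when the available-data estimate is most in doubt, the plan names no analysis.

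At stake is the credibility of the main estimate. Some withdrawal routes (adverse events, worsening, non-compliance) can depend on treatment. If participants lost from the inulin arm would have responded less than those observed, the observed difference would be too large, and the plan as written might offer no quantitative check.

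**Working it through.** **Inputs from the Sample size calculation section.** Expected change 12.5 points (inulin) and 2.5 points (placebo), difference 10, common SD 15, two-sided 0.05, 80% power, 36 per group, about 10% dropout, 40 per group.

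**Step 1: reproduce the plan's figure.** With the normal approximation, n = 2 × (1.96 + 0.84)² × 15² / 10² = 35.3, which rounds up to 36 per group. The exact t-test calculation gives 35.96 at the stated effect size of 0.67. Dropout: 36 / (1 − 0.10) = 40. The sample size reproduces, and this point does not change it.

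**Step 2: how many may be excluded.** 40 − 36 = 4 per arm, so about 8 of 80. The dropout allowance restores the number analysed. It protects power, not freedom from bias.

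**Step 3: the bias formula.** Let m be the missing share in an arm and s the shortfall, meaning the observed participants' mean change minus the mean change the missing participants would have had. Then

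bias in the difference = m(inulin) × s(inulin) − m(placebo) × s(placebo).

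The documents give no value for s and no dropout rate by arm, so what follows is an illustration under assumptions.

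**Step 4: placebo-like change in the missing inulin participants.** Assume that the true mean over all randomised inulin participants is 12.5, that missing ones change by 2.5, and that missing placebo participants resemble observed ones.

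- 10% missing: 12.5 = 0.90x + 0.10 × 2.5, so x = 12.25 / 0.90 = 13.61. The observed difference is 13.61 − 2.5 = 11.11 against a true 10, a bias of about 1.1 points.
- 15% missing (assumed): 12.5 = 0.85x + 0.15 × 2.5, so x = 12.125 / 0.85 = 14.26, a bias of about 1.8 points.
- Equal missing share and equal shortfall in both arms: the two terms in Step 3 cancel and the bias is 0.

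**Step 5: a second way of anchoring.** Suppose instead that the observed participants show the planned 10-point difference and the missing inulin participants fall short by 5 to 12.5 points. The bias is 0.10 × 5 = 0.5 to 0.10 × 12.5 = 1.25 points at 10% missing, and 1.0 to 2.5 points at 20% missing.

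**Step 6: scale.** With 36 per group the standard error is 15 × √(2/36) = 3.54, and the smallest significant difference is 1.994 × 3.54 ≈ 7.05 points. A bias of 1.1 is about 0.3 standard errors (1.11 / 3.54). That is modest, but it could matter for a borderline result.

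**The case against.** The best defence is that the set is stated openly, so the quarrel over the label is partly one of terms. Imputation by chained equations normally assumes missing at random, so running it where that is plausible is coherent. The article condenses a full protocol that is not shown, and a statistical analysis plan may hold more detail. Analysts are blinded to which group is which, which limits the scope for a self-serving judgement.

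Much of this stands, and it rules out several stronger readings that a reader might infer.

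- *That the estimate describes only people who completed treatment.* It does not. The set depends on having samples, not on adherence. Participants who stop the product are asked to continue follow-up, and those who give a Week 6 sample are analysed.
- *That unequal, tolerance-related loss is to be expected.* The gastrointestinal events are listed for the study products in general, the risk is called low, and no rate by arm is given. Such loss is possible, not shown.
- *That the bias would be 1.4 points at 10% loss or 2.2 at 15%.* Those figures follow from giving missing inulin participants no change at all (12.5 / 0.90 = 13.89; 12.5 / 0.85 = 14.71), which puts them below the plan's own placebo change of 2.5. If missing placebo participants are also given zero change at 10% loss, placebo rises to 2.5 / 0.90 = 2.78 and the net bias is again 1.39 − 0.28 = 1.11.
- *That the rule is reversed, or that no check is planned.* The rule is incomplete rather than reversed. Missingness will be examined and imputation may be run. Mixed models for repeated measures are also planned, and Table 1 lists the primary measure at Weeks 2, 6 and 10. That sentence sits with the secondary outcomes, so its reach to the primary measure is unclear. It is not offered as a missing-data analysis.

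What the defence does not remove is that the article itself fixes the label, the set and the condition. This is a stated rule that needs correcting, not detail left for another document.

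**Conclusion.** The point holds on the text. The primary analysis is an available-data analysis carrying an unqualified intention-to-treat label, and about 8 of 80 randomised participants may be outside it on the plan's own dropout allowance. The one missing-data sensitivity analysis of the primary outcome depends on a judgement that observed data cannot verify, with no analysis stated if that judgement is negative.

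The size of any bias is not known. Under the placebo-like assumption it is about 1.1 points at 10% loss in the inulin arm and about 1.8 at 15%, against a planned difference of 10. It is 0 if loss and shortfall are equal between arms. These figures rest on assumed outcomes for unobserved participants and, for 15%, on an assumed loss. Confidence is high for the label and the conditional rule, and does not extend to any claim that the result will be biased. This should be corrected, but it does not undermine the design.

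**What to change.** 1. Keep the planned primary test, and describe its set as randomised participants with available baseline and Week 6 data, analysed as randomised (complete-case or modified intention-to-treat). Align the opening sentence of the Statistical analysis section with this.
2. Delete the condition on imputation. Always report multiple imputation over all randomised participants beside the primary result. Use variables already collected or known: arm, site, baseline and Week 10 abundance, recorded adherence and adverse events.
3. Prespecify one sensitivity analysis that departs from missing at random: either a delta adjustment or a reference-based analysis giving missing inulin participants a placebo-like change.

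Making imputation the primary estimate is not required. That would be a trade-off, not a correction.

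Cost: revised wording through the amendment route in the Ethical considerations section, a little more analysis work, and possibly a slightly wider interval in the sensitivity results. No new data are needed. The Trial status section reports that no outcome analyses had been done at submission, so the change can still be made before results are seen.

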### Safety monitoring

Adverse events (AEs) will be recorded throughout the study period. An AE is defined as any unfavourable or unintended disease, sign, symptom, or abnormal laboratory finding occurring in a participant, regardless of its causal relationship with the study. Expected AEs related to the study products include diarrhoea, soft stools, abdominal bloating, and food allergy; the risk of these events is considered low. Blood samples of 40 mL before the intervention and 60 mL immediately after the intervention will be collected for immunological analyses, and the risk of anaemia is considered very low. If an AE occurs, the investigators will provide appropriate medical care and record the event in the medical records. The study product may be discontinued if necessary. Participants may be withdrawn if they request withdrawal, become ineligible after enrolment, experience an AE or worsening of symptoms that makes continuation inappropriate, substantially deviate from the protocol, fail to comply with the intervention, or if the principal investigator judges that continuation is difficult. Participants who discontinue the study product will be asked to continue scheduled follow-up assessments where possible.

Trial continuation will be reviewed if important safety or efficacy information becomes available, recruitment is judged to be extremely difficult, the study objective is achieved before the planned sample size or study period is reached, or protocol changes requested by the ethics committee cannot be implemented. If the ethics committee recommends or instructs termination, or if the principal investigator decides to suspend or terminate the study, the reason will be promptly reported to the ethics committee and the head of the study institution.

In the event of study-related harm, medical care will be provided through the usual health insurance system.

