### Blinding

A blinding officer, independent of the allocation manager and enrolling investigators, will be responsible for ensuring the indistinguishability of the study products. The blinding officer will prepare a correspondence table linking sequential product serial numbers, the randomisation order, and product allocation codes (inulin or maltose). Based on this table, the blinding officer will label all study product sachets with their respective allocation codes only, so that neither participants nor investigators can identify the contents.

The correspondence table will be kept securely by the blinding officer and will not be disclosed to any other study personnel until unblinding. Unblinding will occur only in the event of a medical emergency requiring knowledge of the allocated treatment for appropriate clinical management of the individual participant. Full unblinding of all participants will be performed only after the database is locked and the analysis population and case eligibility decisions have been finalised.

Participants, enrolling investigators, outcome assessors, and data analysts will remain blinded throughout the study. During data analysis, group assignments will be coded (e.g., Group A and Group B) so that analysts remain unaware of which group received inulin and which received placebo. Unblinding of the data analysts will occur only after the primary analysis has been completed and the results have been locked.

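### Withdrawal for non-compliance, deviation or later ineligibility can remove randomised participants from a primary analysis that is labelled intention-to-treat but limited to those with Week 6 data

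*Protocol article*

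**What the plan says.** Three sections of the protocol article bear on who is in the primary analysis.

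- **Statistical analysis.** The general rule is "All analyses will follow the intention-to-treat principle". The primary set is then defined: "The primary analysis will include all randomised participants with available baseline and Week 6 primary outcome data, according to the intention-to-treat principle". For missing outcomes: "If missingness is judged to be at random, multiple imputation using chained equations will be performed as a sensitivity analysis".
- **Safety monitoring.** The withdrawal rule opens "Participants may be withdrawn if they request withdrawal, become ineligible after enrolment", goes on to adverse events and worsening symptoms, and ends with participants who "substantially deviate from the protocol, fail to comply with the intervention, or if the principal investigator judges that continuation is difficult". Stopping the product is mentioned separately, just before this rule. Just after it comes: "Participants who discontinue the study product will be asked to continue scheduled follow-up assessments where possible".
- **Blinding.** Full unblinding takes place "only after the database is locked and the analysis population and case eligibility decisions have been finalised".

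The article does not say whether being withdrawn means leaving the product or leaving the study. Nor does it say whether a withdrawn participant's Week 6 sample is still collected.

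**The concern.** Non-compliance, protocol deviation and loss of eligibility after enrolment all happen after randomisation, and the assigned product can influence them. An intention-to-treat analysis should be unaffected by them. Here they are grounds on which an investigator may end participation, and the primary analysis keeps only people who have a Week 6 measurement. One section can therefore remove people whom the other claims to keep.

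The route is realistic. Product intake is recorded daily (Concomitant treatments), so non-compliance will be seen. The expected product-related events are mostly bowel symptoms, so tolerance and adherence may differ between inulin and maltose. Recent antibiotic use and hospitalisation are exclusion criteria, and either could occur after enrolment. Blinding does not protect against selection that arises from the product's own effects.

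At stake is what the primary result estimates. If poor adherers leave the inulin arm, the estimate moves from the effect of being assigned inulin towards the effect among those who take it, while still being reported as intention-to-treat.

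**Working it through.** **Step 1: the plan's own figures.** Inputs from Sample size calculation: expected change +12.5 points on inulin and +2.5 on placebo, difference 10, SD 15, two-sided alpha 0.05, power 80%, dropout about 10%.

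- Normal approximation: n = 2 × (1.960 + 0.842)² × 15² / 10² = 35.3, so 36 per group.
- Noncentral t with the stated effect size of 0.67: 36 per group, power 80.05%.
- Dropout: 36 / 0.90 = 40 per group.

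The plan's 36 and 40 are reproduced. The sample size is not the problem.

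**Step 2: who is in the primary analysis under the text as written.**

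| Participant | Week 6 sample | Primary analysis |
|---|---|---|
| Poor complier or deviator who stays in the study | yes | in, as randomised |
| Stops product, agrees to continue assessments | yes | in, as randomised |
| Withdrawn after the Week 6 sample | yes | in, as randomised |
| Withdrawn from the study before Week 6 for non-compliance, deviation, ineligibility or discretion | no | out |

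Only the last row is a loss, and it follows from an investigator's decision about post-randomisation conduct. Multiple imputation is a sensitivity analysis, run only if data are judged missing at random. A model without adherence in it would tend to give withdrawn non-compliers the responses of those who stayed.

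**Step 3: illustration of size.** The article gives no non-compliance rate, so the share w of the inulin arm that does not comply is assumed. Non-compliers are assumed to respond like placebo (+2.5), and the SD is held at 15.

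Effect as assigned = (1 − w) × 12.5 + w × 2.5 − 2.5 = 10 × (1 − w).

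If all of these participants are withdrawn with no Week 6 sample, the analysis estimates 10 instead. The ratio is 1 / (1 − w). Power is for a two-sided t-test with all 40 per arm measured and analysed.

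| w | Effect as assigned | Effect if all are removed | Overstatement | Power, all 40 per arm analysed |
|---|---|---|---|---|
| 5% | 9.5 | 10.0 | 5% | 79.9% |
| 10% | 9.0 | 10.0 | 11% | 75.5% |
| 15% | 8.5 | 10.0 | 18% | 70.6% |
| 20% | 8.0 | 10.0 | 25% | 65.4% |

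For w = 10%: 0.9 × 12.5 + 0.1 × 2.5 − 2.5 = 11.25 + 0.25 − 2.5 = 9.0.

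If only half of those 10% are withdrawn, the analysed inulin arm is 90/95 compliers. The estimate is then 10 × 90/95 = 9.47, an overstatement of 9.47 / 9.0 − 1 = 5%.

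**The case against.** A reader might infer that the withdrawal rule turns the primary analysis into a per-protocol one. The text does not support that. The primary set is defined by data availability alone, and no section excludes a non-complier or deviator who has both samples. Such a person is analysed as randomised, which a per-protocol analysis would not allow.

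Further points on the plan's side:

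- **Withdrawal is permissive.** Participants may be withdrawn, and the article sets no adherence threshold that triggers it.
- **The follow-up sentence may cover them.** Someone withdrawn for non-compliance has in effect also stopped the product, so the request to continue assessments can be read to include them. This reading is fair but not secured. The section treats stopping the product and withdrawing the participant as separate acts, attaches the request to the first only, and qualifies it. Two sites could act differently.
- **Finalising the analysis population and case eligibility before unblinding is a safeguard.** That is right, and the sentence does not say that anyone is excluded for compliance. It does leave open a second point at which randomised participants could be removed.
- **The size is hypothetical.** This stands. The illustration needs every non-complier to respond like placebo, be withdrawn and give no sample. The 20% row is twice the plan's all-cause dropout allowance. The plan also does not restrict its +12.5 points to compliers. If 10 points is already the effect as assigned, then at w = 10% the complier effect is 10 / 0.9 = 11.1. The relative overstatement is again 11%.
- **The full protocol is a supporting file not seen here.** Detail left to it is no fault of the article. The point rests instead on two rules that the article does state and that work against each other.

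**Conclusion.** The point holds in limited form. The article states a rule that lets investigators end participation for non-compliance, substantial deviation, later ineligibility or discretion. It also states a primary set that loses anyone without a Week 6 sample, and labels that set intention-to-treat. It is an available-case analysis that can drift towards per-protocol if the rule is used before Week 6. The only stated safeguard in the analysis is a conditional imputation sensitivity analysis.

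The direction of concern is overstatement of the effect of being assigned inulin. The amount is unknown. The figures of 9.0 against 10.0 points (10% non-compliance) and 8.0 against 10.0 (20%) rest on assumed rates, a placebo-like response in non-compliers and removal of all of them. They show sensitivity and do not predict bias. The documents do not show that such withdrawals will be common or will differ by arm. They show only that the rules permit them and that the expected events make a difference between arms plausible. The matter should be corrected, and it does not undermine the design.

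**What to change.** Reconcile the Blinding, Statistical analysis and Safety monitoring sections:

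1. Separate discontinuing the product from withdrawing from the study, and say which one each listed reason leads to.
2. State that non-compliance, deviation and ineligibility arising after enrolment do not by themselves end data collection. The scheduled Week 6 and Week 10 samples are still sought unless the participant withdraws consent.
3. State that all available data are analysed as randomised, whatever the adherence, deviation or later eligibility, and that the case eligibility decisions before unblinding do not remove participants on these grounds.
4. Describe the primary set as randomised participants with available data, and place any analysis of compliers as secondary.

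The adverse-event and symptom-worsening grounds for stopping stay as they are, and no clinical rule is proposed here. If the full protocol already makes this separation, only the article needs aligning.

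The cost is a wording amendment, some effort to keep visits that are already scheduled, and slight dilution of the estimated effect because non-compliers stay in. Recruitment is planned to 31 March 2029, so an early amendment would cover most participants.
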